### Plans to give access to the full protocol, participant-level data, and statistical code {31c}

Data derived from this investigation will be provided to proficient scholars with an academic concern in keloid treatment. We plan to submit dataset in the National Library of Medicine repository. Any shared data or samples will be coded, and no protected health information will be included. Authorization of the dataset solicitation is mandatory prior to sharing any data with the inquiring entity. The data will be made available for up to 24 months, commencing 2 years after the publication of the results. Requests for extensions will be evaluated on a case-by-case basis. Trial individual participant data (IPD) can be requested by eligible researchers who are conducting independent scientific research.

## Oversight and monitoring

### Composition of the coordinating centre and trial steering committee {5d}

The study’s principal investigator and research physician will collaborate in developing and executing the research plan, including protocol preparation and revisions. Additionally, they will provide an investigator brochure (IB), case report forms (CRFs), and informed consent forms. The assessment assessors will receive training from the principal investigator and other research physicians, who will also disseminate the study results. The trial management committee, composed of the principal investigator, research physicians, data manager, and administrator, will oversee the day-to-day running of the trial, including study planning, risk reporting to the ethics committee, randomisation, and data verification. The data manager will maintain the trial IT system, data entry, verification, and statistical analysis. The committee will meet at least three times: before enrolment, during the study, and at the end to determine the necessary steps in the trial.

The trial steering committee is an independent group comprising a clinical consultant, medical statistician, clinical monitor, regulatory authority, and patient representative. Their role is to ensure that the study runs smoothly and efficiently by reviewing the final protocol and any necessary changes during the study. The committee monitors the trial’s progress, adherence to the protocol, and patient safety, ensuring ethical requirements, regulations, and standards are followed. They also provide that the necessary documentation is available and that all collected data is accurately recorded. The committee holds meetings prior to study enrolment and during the middle of the study.

### Composition of the data monitoring committee, its role and reporting structure {21a}

Not applicable. Based on the literature review conducted by Sydesand et al. [73], it has been determined that the data monitoring committee (DMC) is unnecessary for this trial since the study is of short duration (12 weeks) and presents minimal risk to participants who enrol. Throughout the study, the sponsor-investigator will ensure that all planned activities are carried out correctly and that any shortcomings are quickly identified and fixed. Thus, a clinical monitor from the education and research unit of Syafira Hospital is accountable for supervising the study’s progress and protecting patients’ safety and rights. The clinical monitor ensures that ethical requirements, regulations, and standards are followed, essential documentation is accessible, and all gathered data is recorded accurately.

### Adverse event reporting and harms {22}

According to a recent study, the new therapy intervention has been deemed safe and does not cause any irritations [49]. Yet, there may be other unknown side effects that could arise during the study. The intralesional injection of triamcinolone acetonide may lead to temporary side effects, including pain, inflammation during injection, bleeding, contact dermatitis caused by preservatives in the injection fluid, infection (rare), and anaphylaxis reactions (infrequent). Long-term side effects may include skin atrophy, telangiectasia, hypo- and hyperpigmentation, and steroid acne (rare) [20]. Participants need to report any adverse events during the study, and researchers need to document them in an adverse event form. Any adverse events will be handled appropriately, following clinical procedures, and reported to the trial steering committee and Medical and Health Research Ethics Committee (MHREC) at Universitas Gadjah Mada.

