### Intervention description {11a}

Forty-six eligible adolescents with keloid will be randomly assigned to the 5% losartan potassium loaded in ethosomal gel (5% LEG) group (*n* = 23) and active control of triamcinolone acetonide 10 mg/ml (TAC 10mg/ml) groups (*n* = 23). Ethosomal gel bearing 5% losartan potassium will be applied twice daily on the keloid with the rule of fingertips unit (FTU) [50], and 10 mg/ml TAC will be injected intralesionally in the keloid every 2 weeks for 12 weeks with the rule of 0.1 mg/cm^2^ [51]. With a Good Manufacturing Practise (GMP) certificate, the Dion Farma Abadi company will provide 5% LEG. The study patients will receive the intervention gel monthly during the study visit. Ten milligrams per millilitre triamcinolone acetonide (Flamicort®) used in the study is manufactured by Dexa Medica. Our trial has four study visits, i.e. before the intervention or baseline, after 4, 8, and 12 weeks.

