### Criteria for discontinuing or modifying allocated interventions {11b}

If any signs of side effects, such as allergies or worsening complaints, are observed during intervention treatment, it will be discontinued immediately. Similarly, in the control injection treatment, the dose will be reduced or stopped if any allergic side effects or skin atrophy are detected or the participant expresses unwillingness to continue the study.

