### Strategies to improve adherence to interventions {11c}

We will inform study patients how to use their gel treatment and the schedule of injections, and phone calls will follow them weekly. The compliance evaluation will depend on the quantity of gel left in the tubes and the adherence to injection visit schedules.

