The colour images will be captured using dermoscopy equipment from Heine® iC1 Germany, followed by image analysis. Dermoscopy is employed to capture colour images from three discrete regions, specifically focusing on the edges and central region. This process is iterated for precision, and subsequently, ImageJ image analysis computes the average colour quantification of the captured images. The same proficiently trained assistant will capture colour images using dermoscopy consistently during the entire duration of the study. Our team will utilise digital photography (Sony®α6000 Japan) and ImageJ image analysis software to examine the surface area. A trained assistant will take pictures of the keloid with appropriate camera lighting, and a ruler will be included in the shot to confirm the scale in ImageJ. The surface area changes will be measured in centimetres squared and evaluated at four different time points throughout the study.

A dedicated computer IT assistant, consistent throughout the study, will measure colour degrees and surface areas using ImageJ to maintain consistency.

High-frequency ultrasound (Hitachi® Arietta s60 Japan) will be employed to assess keloid thickness. The linear probe will be operating at frequency of 5–12 MHz [50]. Throughout the study, the same radiologist will consistently measure the thickness of the keloid in centimetres, specifically assessing it at the same three points as during the initial measurement. Subsequently, the obtained measurements will be averaged for analysis. The pliability of keloids is measured using a manual tonometer called durometer type oo (Tecklock® Japan). A trained assistant will use the tonometer on three different areas of the keloid and calculate the average in durometer units displayed on the device. During the study, we will also monitor for any potential side effects arising from the interventions.

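### Injection participants are seen in person twice as often as gel participants and equal questioning about adverse events is not set up, so transient events could be recorded more often on triamcinolone at equal true rates

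*Protocol article*

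**What the plan says.** The section on adverse event reporting (item 22) gives the method of collection: "Participants need to report any adverse events during the study, and researchers need to document them in an adverse event form". Outcomes (item 12) adds "During the study, we will also monitor for any potential side effects arising from the interventions", without a method or timetable.

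Intervention description (item 11a) sets the contacts. For the control arm, "10 mg/ml TAC will be injected intralesionally in the keloid every 2 weeks for 12 weeks". For the gel arm, "The study patients will receive the intervention gel monthly during the study visit". For both arms, "Our trial has four study visits, i.e. before the intervention or baseline, after 4, 8, and 12 weeks".

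The section on adherence (item 11c) adds remote contact: participants are told "how to use their gel treatment and the schedule of injections, and phone calls will follow them weekly". This covers both arms. The section goes on to judge compliance by leftover gel and by attendance for injections, and does not say what the calls ask.

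The section on blinding (item 17a) states that participants and staff cannot be blinded; outcome assessors and the data analyst are.

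**The concern.** When harms are recorded mainly because a participant mentions them, the number recorded depends on how often, and how, someone gives the participant the occasion to do so. Here one arm has extra face-to-face contacts at weeks 2, 6 and 10. An itch or redness that comes and goes between two monthly visits has fewer chances of reaching the adverse event form on the gel than on the injection. Both sides of the conversation know the treatment, so expectations can add to the imbalance.

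The stake is the comparison of harms, not efficacy. Harms are not among the listed primary or secondary outcomes. However, the side effects of triamcinolone are part of the case for testing a gel (Background, item 6a, and choice of comparators, item 6b), and the Discussion expects the gel to be comfortable to use. Readers will compare the two adverse event columns. Any imbalance in collection would make the gel look better tolerated than it is relative to the injection.

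**Working it through.** The plan states no adverse event rate or detection rate, so it has no figure of its own to reproduce. The check is a count of contacts followed by a simple capture model.

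**Contacts after baseline, to week 12 (item 11a)**
- Triamcinolone: weeks 2, 4, 6, 8, 10, 12 = 6. Week 12 is a study visit whether or not an injection is given then.
- Gel: weeks 4, 8, 12 = 3.
- Ratio in person: 6/3 = 2. With the weekly calls (item 11c), both arms have some contact at least every 7 days.

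**Assumptions (not in the documents)**
- Onset is uniform over the 84 days, with equal true rates in both arms.
- An event can be captured for *w* days after onset, with *w* from 3 to 14.
- A visit captures every event still in its window. A call captures a fraction *s* of them, from 0 to 1.

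**Visits only (*s* = 0).** Capture = min(*w*/interval, 1), with intervals of 14 and 28 days.

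| *w* (days) | Triamcinolone | Gel | Ratio |
|---|---|---|---|
| 3 | 3/14 = 0.214 | 3/28 = 0.107 | 2.00 |
| 7 | 7/14 = 0.500 | 7/28 = 0.250 | 2.00 |
| 14 | 1.000 | 14/28 = 0.500 | 2.00 |
| 21 | 1.000 | 21/28 = 0.750 | 1.33 |
| 28 | 1.000 | 1.000 | 1.00 |

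The last two rows lie outside the assumed range. They show that the imbalance fades as events last longer.

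**Adding the weekly calls, *w* = 7.** Each event meets exactly one weekly contact. That contact is a visit with probability 6/12 on triamcinolone and 3/12 on gel. Capture is 0.50 + 0.50*s* against 0.25 + 0.75*s*.
- *s* = 0.25: 0.625 / 0.4375 = 1.43
- *s* = 0.50: 0.750 / 0.625 = 1.20
- *s* = 0.75: 0.875 / 0.8125 = 1.08
- *s* = 1: 1.00 / 1.00 = 1.00

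For *w* = 3, both probabilities are multiplied by 3/7, so the ratios are the same.

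**Adding the weekly calls, *w* = 14.** On triamcinolone a visit always falls in the window, so capture is 1. On gel a visit does so half the time; otherwise two calls do. Capture is 0.5 + 0.5[1 − (1 − *s*)²].
- *s* = 0.25: 1 / 0.719 = 1.39
- *s* = 0.50: 1 / 0.875 = 1.14
- *s* = 0.75: 1 / 0.969 = 1.03

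**In participants.** Assume a true rate of 30% in each arm of 23 (6.9 participants) and *w* = 7.
- Calls capture nothing: 6.9 × 0.50 = 3.5 against 6.9 × 0.25 = 1.7 recorded (15.0% against 7.5%).
- Calls half as good as visits: 6.9 × 0.75 = 5.2 against 6.9 × 0.625 = 4.3 (22.5% against about 18.8%).
- Calls as good as visits: 6.9 against 6.9.

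**The case against.** The strongest reply is that contact is not really unequal. Everyone is telephoned weekly, the trial undertakes to monitor side effects, and participants are asked to report any event during the study, so one at week 4 can describe a rash from week 3. If the calls work half as well as visits, the ratio is already down to 1.14 to 1.20; at three quarters it is 1.03 to 1.08. A ratio of 2 needs calls that detect nothing and participants who do not mention past events. All of this stands, and it is why the conclusion is that differential recording could occur, not that it would.

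It can also be said that call scripts and event forms belong in the full protocol and case report forms, and that the schedule in Fig. 1, which is not shown, may list adverse event checks. That is possible. But checks at the common visits alone would leave the extra contacts at weeks 2, 6 and 10 in place. The imbalance comes from the reporting method and visit schedule that the article itself states.

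Three stronger readings are tempting and are not supported:
- **The calls have no part in collecting events.** The adherence section does not say so; it is silent on what is asked.
- **A reaction to the gel could not lead to stopping before week 4.** Item 11b reads "If any signs of side effects, such as allergies or worsening complaints, are observed during intervention treatment, it will be discontinued immediately". Worsening complaints can be voiced on a weekly call or volunteered at any time, and nothing makes the rule wait for a visit.
- **Events found at the injection-only visits should be kept out of the comparison.** Item 22 lists pain, inflammation during injection and bleeding among the effects of the injection. These arise at those visits, and removing them would hide genuine harms of triamcinolone.

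**Conclusion.** The point holds in a limited form. The documents fix a 2:1 difference in post-baseline in-person contact (6 against 3), rely on participant reports, leave participants and staff unblinded, and do not establish equal elicitation through the calls or the monitoring. Transient events could therefore be recorded more often on triamcinolone at equal true rates. The apparent ratio lies between 1.0 and 2.0 for windows of 3 to 14 days. Where it falls depends on what the calls ask and how much participants volunteer, neither of which the article states. The windows, the call sensitivity and the 30% rate are assumptions.

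A reader might infer that the trial is bound to show a doubling of events on triamcinolone. That is only the extreme end of the range. Atrophy, telangiectasia and pigment change would normally still be visible at the 4-weekly visits, so the concern is mainly with itch, redness, irritation and similar short-lived complaints. The POSAS analysis is little affected.

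**What to change.** In the sections on adherence (item 11c) and adverse event reporting (item 22), state that the weekly calls and the common visits at weeks 4, 8 and 12 put the same short scripted adverse-event questions to both arms. Enter the answers on the adverse event form with date, severity and the contact at which the event was found. Keep the scripted calls in the injection arm in weeks 2, 6 and 10 as well, so that an event first seen at an injection visit can also be elicited in the common way.

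Report all events in full, including those found at injection-only visits. Show the between-arm comparison of harms twice: for all events, and for events elicited at contacts common to both arms. The first keeps the procedure-related harms; the second compares the arms under equal questioning.

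The cost is a call script and a page of the case report form, using calls already planned. The small downside is a few more minutes per call and more minor events recorded. Treatment and visit schedules do not change.

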### Frequency and plans for auditing trial conduct {23}

The Indonesian Food and Drug Authority will oversee the auditing of trial conduct as a regulatory authority and will be included in the steering committee. This auditing process will be independent of the investigator and sponsor, and it will take place in the early stages and in the middle of the trial to ensure that subjects are protected and that regulations, including the principles of Good Clinical Practices (GCPs), are being followed.

### Plans for communicating important protocol amendments to relevant parties (e.g. trial participants, ethical committees) {25}

If any changes to the study protocol could impact the safety and well-being of participants, we will ensure that all relevant parties are informed. This includes the ethics committee, trial registry, steering committee, journal, and participants. Before conducting the trial, any modifications that concern patients’ safety and well-being will require confirmation from the MHERC at the Faculty of Medicine, Public Health, and Nursing at Universitas Gadjah Mada Yogyakarta and the steering committee. Any modifications will be reported to ClinicalTrials.gov as a registry board, and participants will be notified if there are any changes to interventions and outcome assessments. Finally, the Trials journal will serve as the publication site for the modifications.

### Dissemination plans {31a}

The research results will be shared with the public through journal publications. At the same time, research reports will be submitted to the funder Universitas Gadjah Mada. Furthermore, the research findings will be reported to the institution in charge of clinical registration through Clinicaltrial.gov. This marks the final step of the registration process.

## Discussion

Based on the previous review [14], it has been found that angiotensin II can initiate the formation of keloids and hypertrophic tissue through various mechanisms. It can lead to vascular dysfunction due to the effects of vascular endothelial growth factor (VEGF) and basic fibroblast growth factor (bFGF) II, which can both promote angiogenesis. However, VEGF can also contribute to fibrosis development through various means, such as activating signals that stimulate growth, movement, and collagen production by myofibroblasts through TGF-β1 signals and extracellular signal-regulated kinase (ERK) [72]. Another mechanism is increased IL-6, which plays a role in the process of fibrosis, strengthens the deposition of extracellular matrix, type I collagen, and stimulates other fibrogenic mediators, including TGF-β and tissue inhibitor matrix metalloproteinase (TIMP) [74]. Furthermore, angiotensin II may increase TGF-β and connective tissue growth factor (CTGF) expression. TGF-β has an essential role in the stimulation and synthesis of the extracellular matrix. It causes the formation of scar tissue through the TGF-β signalling pathway. Angiotensin II through the AT1 receptor will activate collagen expression through the TGF-β/small mothers against decapentaplegic (SMADs) signalling pathway [73, 75]. Stimulation of keloid fibroblasts, hypertrophic scar tissue, and normal tissue by TGF-β will cause an increase in the expression of CTGF, which becomes a fibrogenic mediator on angiotensin II [76]. Ultimately, the mechanism involved is increasing the expression of tissue inhibitors of matrix metalloproteinases-1 (TIMP-1), which functions to degrade, inhibiting the work of matrix metalloproteinases (MMPs) [75]. Angiotensin II binds to AT1R in melanocytes and will increase melanogenesis through the protein kinase C (PKC) pathway [77].

Losartan potassium is among the initial types of angiotensin II type 2 receptor blockers (ARBs) that have undergone extensive research regarding fibrosis. Losartan falls under the ARB drug class, which shares similar effects with other drugs of the same class but has a distinct molecular effect that sets it apart from others. The molecular effects of losartan in the process of fibrosis are that it can reduce the production of chymase, which plays a role in the formation of angiotensin II as in mice with cardiac fibrosis [78] and can modulate prostaglandins which play a role in the process of fibrosis [79]. Losartan potassium inhibits prostaglandin thromboxane A2/prostaglandin endoperoxide H2 (TxA2/PGH2) receptors on blood vessels and platelets which plays a role in the process of fibrosis by reducing the production of cyclic adenosine monophosphate (cAMP), which acts as an anti-fibrosis through the inhibition of SMADs [79] so that the process of fibrosis increases. Losartan also can increase the production of prostaglandin E2 (PGE2), which has an anti-fibrotic effect, and PGE2 keloids have decreased production by fibroblasts [80–82]. Research on losartan administration to rats with pulmonary fibrosis showed increased PGE2 production [83]. Losartan potassium can be found on the market at an affordable price compared to other ARB classes.

One of the advantages of administering topical drugs is that they are more comfortable in application because they do not cause side effects of pain, have high adherence, and can be applied by the patient himself [23]. Problems in topical drug delivery that must be addressed so that drugs can work optimally are the physicochemical characteristics of drugs and physiological barriers on the skin [84] as well as drug formulations that can affect penetration ability [35]. Drug formulations can affect penetration ability, so the delivery strengthening strategy is chosen through passive methods using nano-sized carrier formulations [40] using an ethosome suitable for keloid skin structures [39]. The choice of this gel-based drug carrier is due to its minimal effect on the stability of the lipid nanovesicles. It can improve the permeation rate of the drug in the skin [85], apart from convenience in the application. Determination of the percentage of 5% losartan potassium selected in the preparation was based on previous studies [29, 31]. Based on the suspected mechanism of action in previous studies, we hypothesised that 5% LEG has good efficacy for keloid treatment and is comfortable to use.

This study has several strengths, including a randomised, unpaired group, single-blind, and active-control design. Furthermore, the effects of 5% LEG are examined from both subjective and objective perspectives. Assessing outcomes in a clinical environment with limited resources has proven practical and efficient with the available evaluation tools. While the research conducted has its strengths, there are also some weaknesses. One such area for improvement is that the study does not include a comparator of 10 mg/ml TAC and 5% LEG combination therapy group. Additionally, the study only measures clinical outcomes and does not confirm any evidence from biomarker changes. Furthermore, the study is limited in duration, and it will be beneficial to extend the application of 5% LEG to observe its impact on keloids over a more extended period. This trial will provide scientific evidence favouring using 5% LEG for managing keloid.

